## Abstract

**Background:**

Informal caregivers (CGs) of patients with Alzheimer’s disease are at risk of suffering from psychological and physical weakening. Several psychoeducational interventions have been designed to prevent stress and burden of caregivers. In France, despite health authorities’ recommendations, to our knowledge there is no rigorously assessed Web-based psychoeducational program to date.

**Objective:**

The objective of our study was to assess the efficacy of a French Web-based psychoeducational program (called Diapason) with an unblinded randomized clinical trial.

**Methods:**

In this protocol, 80 informal caregivers of patients followed at Broca Hospital are recruited offline and randomized in the experimental condition (EC) or the control condition (CC). The volunteers in EC have to visit a closed online user group at least once a week and validate one new session of this fully automated Web program, during 12 weeks. Each week a new thematic is added to the website. The participants in the CC receive usual care, and have access to the Diapason program after their participation (6 months). Face-to-face evaluations for both groups are planned every 3 months (M0–M3 and M6). The main objective of this program is to provide CGs with information on the disease process, how to prevent psychological strain (using anticipation and relaxation techniques), and offering a virtual space (forum) to discuss with other caregivers. The primary outcome of this study is the self-perceived stress, while self-efficacy, burden, depression, and self-perceived health status are defined as secondary outcomes. Other variables that might have an impact on the program efficacy are collected.

**Results:**

This protocol was accepted for funding. The enrollment began in October 2011, and participants currently recruited will finish their evaluations in January 2014. The results are expected for June 2014.

**Conclusions:**

Findings might provide empirical evidence on: (1) the feasibility of an Internet-based program in the French context, (2) the effectiveness of a Web-based program for informal caregivers, and (3) the identification of caregivers who will benefit from this type of intervention.

**Trial Registration:**

Clinicaltrials.gov NCT01430286; http://clinicaltrials.gov/ct2/show/NCT01430286 (Archived by WebCite at http://www.webcitation/6KxHaRspL).

## Introduction

### Background

Informal caregivers (CGs) of patients with dementia have an important role in the prevention of patients’ institutionalization. Unfortunately, CGs are prone to high levels of stress and are at higher risk of weakening mental and physical health, lower life expectancy, and lesser economic security than people who are not confronted with such stressful situations [1]. In order to prevent these consequences various programs have been developed for them, which have shown a positive effect on caregivers’ burden, depression, or stress [2-4]. Furthermore, several studies have demonstrated the protective role of resilience and coping factors for this population [5].

The new recommendations following French Alzheimer's Plan 2013 [6] underlined the use of Web-based interventions in order to inform and support family caregivers.

### Distance-Based Interventions

There are many reasons for caregivers to use or to prefer a distance intervention instead of a face-to-face one. In fact, CGs spend a lot of their time in care activities, supporting directly (eg, cooking, housekeeping, supervising their loved ones) or indirectly (eg, doing administrative, financial, or logistic management) their relatives. Furthermore, the time requested for caring increases with the disease progression, and finding time for their own respite can be quite difficult. In fact, several CGs fulfill many roles, such as being parent, grandparent, worker, and friend. Finally, some of them live in remote regions and other CGs do not feel at ease with face-to-face interventions or prefer a flexible time/content intervention [7].

Distance interventions, based on information and communications technology (ICT), appeared in the earlier part of the 21st century in order to propose an alternative intervention to caregivers unable to access health centers delivering face-to-face programs. Distant programs have shown a positive effect on self-perceived stress, burden, depression symptoms, and social support of caregivers [7-14]_._

In the case of caregivers of patients with dementia, several websites exist in France, but these programs have not been, to our knowledge, subjected to a randomized clinical trial.

It is therefore relevant to evaluate the impact of ICT-based or distance-based interventions on the mental and physical health status of caregivers in a controlled experimental study with a French population. It could represent a base for the health care policies and facilitate financial support for these initiatives.

*Diapason* [15] is a fully automated Web-based version of a psychoeducational program, inspired by the group intervention sessions from the geriatric service of Broca Hospital called Aide dans la Maladie d’Alzheimer (AIDMA) program, or in English: Help in Alzheimer’s disease. AIDMA was assessed in a previous study including 167 dyads “patient-caregiver” and showed a significant improvement in disease understanding and in the ability to cope with care-recipients’ disease [16,17]. The difficulty to schedule and attend all sessions (once per week during 12 weeks) for some of the caregivers was the main reason to adapt the program into an Internet-delivered version. Thus, we have adapted and designed a Web-based program in order to improve the accessibility for caregivers.

The purpose of this article is to present the study protocol of a randomized clinical trial designed to evaluate the efficacy of Diapason, a Web-based psychoeducational program for caregivers of patients with Alzheimer’s disease (AD). Our hypothesis is that the Diapason program reduces the caregiver’s perceived stress and burden and enhances his/her self-efficacy and self-perceived health. This study protocol has received approval from the French competent authorities (ie, Agence Française de Sécurité Sanitaire des Produits de Santé, Centre de Protection de Personnes–CPP, Commission nationale de l'informatique et des libertés).

## Methods

### Study Design

This is a pragmatic and unblinded randomized controlled trial (NCT01430286) of a Web-based psychoeducational program for the CGs of patients diagnosed with AD. Two parallel groups are compared. The experimental group receives immediate access to a Web-based program, and the comparison group is given the information usually delivered to the patient by the geriatrician during follow-up consultations. In addition to the baseline visit, two follow-up visits at the hospital are planned at 3 and 6 months.

### Participant Eligibility

Eligible participants are informal French-speaking caregivers (family or not, providing care to the patient at least 4 hours per week) of an AD patient diagnosed at the Memory Center of the Broca Hospital, Paris, France, and who meets the criteria in the Diagnostic and Statistical Manual of Mental Disorders, 4th Edition [18] or National Institute of Neurological and Communicative Disorders and Stroke and the Alzheimer’s disease and Related Disorders Association criteria [19]. To be included in the trial, caregivers have to be 18 years or older or to be able to provide an informed consent, to score 12 or over on the Perceived Stress Scale of 14 items (PSS-14) [20] during screening, and to have a computer with an Internet access at home with an email address regularly used. If participants (CGs) are on psychopharmacological treatment or therapy, they are required to keep the same treatment at least two months before inclusion in the protocol.

### Exclusion Criteria

Exclusion criteria include being a professional or paid caregiver, a volunteer suffering from a physical or mental health status incompatible with patient's care, or following another psychoeducational program.

### Recruitment

Strategies to communicate about the program include flyers and posters in medical waiting rooms of the Memory Center as well as in other places in the Broca Hospital. An information meeting for the hospital staff has been organized before starting the inclusions in order to explain the study protocol. Then, the contact forms are available in every counseling room and in the waiting room.

The participants are recruited either during the follow-up consultation of a patient: (1) the geriatrician/neurologist delivers the general information about the protocol and gives a contact form to fill in and drop off at the Memory Center’s reception desk, or (2) the CGs fill in the contact form available in the waiting room and drop it off at the Memory Center’s reception desk.

One of the two research psychologists previously trained in the protocol contacts the caregiver, checks his/her eligibility criteria and explains the benefits, constraints, and schedule of the protocol. The psychologist gives an information notice to the caregiver and proposes to contact him/her a few days later. If the caregiver agrees with the protocol and meets the criteria for inclusion, the screening session (M0) is scheduled with the caregiver.

### Randomization

A computer-generated randomization list is used to assign the participants in the experimental condition (EC) group or in the control condition (CC) group after assessment with PSS-14 and all the inclusion and noninclusion criteria are checked. Blocking and stratification by gender and relationship (spouses versus nonspouses) were used to generate the randomization list.

### Interventions

#### Experimental Condition

The Diapason program is an adapted fully automated computerized version of a psychoeducational program (AIDMA) created by the Geriatric Service of Broca Hospital. Usability of Diapason program was evaluated in a previous experimental study (pre/post). The study involved the assessment of 30 volunteer participants 60 years or older, with various levels of expertise in Internet use, during a guided visit. After modifications and adaptation of the website, the performances of beginners and experts were similar [21].

Diapason is a free password-protected website. Figure 1 shows the home page. The program is run in twelve thematic weekly sessions organized in the following order: (1) caregiver stress, (2) understanding the disease, (3) maintaining the loved ones’ autonomy, (4) understanding their reactions–how to recognize behavioral and emotional troubles, (5) coping with behavioral and emotional troubles, (6) communicating with loved ones, (7) improving their daily lives, (8) avoiding fall risks, (9) pharmacological and nonpharmacological interventions, (10) social and financial support, (11) about the future, (12) in a nutshell–a summary of Diapason program.

Globally, these twelve sessions cover the following areas: (1) information about AD diagnosis, symptoms, treatment, and progression, (2) how to cope with stressful situations, and (3) information about socioeconomic support and preventive gestures. A new session is available each week, after the validation of the previous session. Furthermore, the website also contains: (1) relaxation guidelines and training videos (based on Schultz’s Autogenic Training and Jacobson’s method) [22,23], (2) stories based on testimonials of caregivers, used to show critical situations and possible solutions to manage them (eg, apathy of patient, caregivers’ isolation), (3) a glossary for the technical words (eg, neuropsychological assessment, aphasia), (4) stimulation guidelines and entertainment activities to do with the patients, and (5) a forum allowing users to establish contact with other caregivers anonymously, express their concerns, discuss solutions to daily problems, and share their feelings and experiences. The participants use nicknames to protect their privacy. A clinical psychologist takes part in discussions if necessary (ie, aggressive or inappropriate comments).

Participants involved in experimental group have to validate one session per week during 12 weeks (about 10 minutes per session), and complete a satisfaction survey corresponding to each session. During the first evaluation (M0) the participant is trained by a psychologist in how to use the website. At the second visit (M3) the participant is requested to provide the satisfaction paper-based survey filled out.

**Figure 1 figure1:**
[figure not shown]
Home page.

#### Control Condition

Participants randomized in the CC group receive usual care. It consists of a geriatric semiannual follow-up appointment during which the caregiver obtains illness information from the geriatrician. The volunteers receive the access code to the Diapason website at the end of their participation in the research protocol. Every participant of the CC group is advised to look for more specific help (ie, that of a psychologist or a physician) when he/she feels it necessary and then to report it to the main investigator.

### Measures and Procedures

#### Participant Recruitment

The physicians of the Memory Center have been informed on the study protocol and have received training in inclusion criteria screening. They provide the caregiver with some information about this study at the end of the consultation with the patient. Then the physician gives a contact form to the volunteers interested in participating in the study. The research psychologist contacts the person, presents the protocol study, and provides the caregiver with the information sheet. When the participant delivers a positive answer, the first visit (M0) at the hospital is scheduled together with the psychologist.

#### Assessment Protocol

The duration of each visit (M0-M3 and M6) is estimated to 90 minutes. The baseline visit is usually conducted as follows:

The research psychologist answers the questions on the information notice and the participant signs the informed consent if he/she agrees.Evaluation with PSS-14 (primary outcome).Randomization if PPS-14 total score is 12 or over.Demographical interview and control questions of caregiver and patient’s variables.Assessment of secondary variables (researcher-administered, and then self-administered surveys).The participants randomized in the EC receive the material (weekly paper-based survey, a journey book, and a user’s manual of the website) and a personal access code to the website. Then, they are trained on how to use the Web-based program.The CC participants are notified that they will receive a website access at the end of their participation to this protocol (6 months after M0).Planning follow-up visits (M3-M6).

For the CC and EC groups, the assessments at M3 and M6 visits are similar, and go as follows: (1) evaluation of caregiver variables (time spent on caregiving, use of respite resources, stressful events, etc) and patient status (hospitalization or other unexpected event occurred in the last three months), (2) measurements with self-administered scales or administered by an interviewer. The measures used in this RCT are summarized in Table 1.

**Table 1 table1:** Overview of measures in the baseline and follow-up visits.

Variables (instruments/measures)		Administration	M0	M3	M6

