#### Secondary Outcomes Measures Administered by an Interviewer

##### Self-Efficacy

The Revised Scale for Caregiving Self-Efficacy was validated in 2002 by Steffen et al [26] and translated into French by Marziali and Garcia in 2011 [27]. This scale offers a simple and effective way to evaluate caregivers’ self-efficacy on: (1) obtaining respite, (2) controlling upsetting thoughts, and (3) responding to disruptive patient behaviors. Each section has five items arranged from easiest to most difficult (based on research results) [26]. For each item the participants choose a score between 0 and 100, based on their degree of confidence for each situation. This scale should be administered by an interviewer [26].

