##### Data Analysis

The Biostatistics and Epidemiology Department of the Hôtel-Dieu Hospital will perform statistical analysis. All the analyses will be conducted according to the intention to treat principle and to handle with missing data; multiple imputations will be used if the missing at random or missing completely at random hypothesis holds. Otherwise sensitivity analysis will be done. No interim analysis will be performed.

A description of the characteristics of the two groups will be performed using percentages for categorical variables and means with standard deviation for quantitative variables. For primary and secondary outcomes, student *t* tests or a Wilcoxon test if required, as well as covariance analysis to take the regression to the mean into account, will be used to compare means between experimental and control groups. Percentages will be compared using chi-square test or Fisher’s exact test if required. Calculations will be performed using SAS software.

Qualitative data obtained during visits M3 and M6 from EG participants’ perception on the program’s utility and satisfaction will be analyzed by Broca’s research team, using thematic analysis [39].

Statistical analysis will exclude data from: (1) caregivers performing less than two thirds of the online program (participant validates fewer than 8 out of 12 sessions), (2) dropouts due to mental or physical state of the caregiver becoming incompatible with this research protocol.

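### The baseline visit randomizes before the interview and the secondary scales, so adjusting secondary outcomes for their M0 scores can bias those comparisons

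*Protocol article*

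**What the plan says.** The Assessment Protocol section gives the M0 visit as a sequence: consent, PSS-14, randomization, interview, secondary scales, and last the experimental-arm material and training or the control-arm notification. The key steps read "Randomization if PPS-14 total score is 12 or over.Demographical interview and control questions of caregiver" and then "Assessment of secondary variables (researcher-administered, and then self-administered surveys").

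The Randomization section agrees. Assignment takes place "after assessment with PSS-14 and all the inclusion and noninclusion criteria are checked"; completion of the other baseline measures is not a condition.

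The sequence is introduced with "The baseline visit is usually conducted as follows", so it describes usual practice and is not an absolute rule. Study Design calls the trial unblinded. Table 1 lists the RSCS, RMBPC, burden (ZBI), health (NHP) and depression (BDI-2) scales as M0 measures. The first two are given by an interviewer; of the RSCS the article says "This scale should be administered by an interviewer".

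For primary and secondary outcomes alike, Data Analysis plans t or Wilcoxon tests, "as well as covariance analysis to take the regression to the mean into account".

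**The concern.** A baseline covariate is safe in a covariance analysis because allocation cannot have influenced it. Here only the PSS-14, and whatever was established at the eligibility check, is certain to precede allocation. The secondary scales are subjective, and two of them are given by an interviewer in an unblinded trial after the arm has been assigned. If knowing the arm moves how a question is put or answered at M0, the two arms' M0 means differ because of allocation. Adjustment then carries part of that difference into the estimated effect.

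The article does not name the covariate, but the stated purpose, regression to the mean, implies the M0 value of the same scale. At stake are the secondary comparisons, mainly self-efficacy and reaction to behavior problems, and the reading of the M0 caregiving variables as pre-randomization characteristics.

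**Working it through.** **The plan's own figure.** The only computed figure is the sample size: a 6-point difference, SD 9, two-sided alpha 0.05, 80% power. The normal formula gives n = 2 × (1.960 + 0.842)² × 9² / 6² = 35.3, so 36 per group (37 with the t distribution). The stated 40 is on the safe side. It is used below only as the number per arm.

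**Order of steps against disclosure**

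| Step at M0 | Relative to randomization | Relative to listed disclosure to the participant |
|---|---|---|
| PSS-14 | before | before |
| Caregiving interview | after | before |
| RSCS, RMBPC (interviewer) | after | before |
| ZBI, NHP, BDI-2 (self-administered) | after | before |
| Experimental-arm material and training, or control-arm notification | after | this is the disclosure |

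The interviewer is thus the clearer route for any influence. The article does not say who obtains the allocation or when, so the interviewer's knowledge of the arm is inferred from the order and the lack of blinding.

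**Size, under assumptions.** The documents give neither a shift nor an M0-to-M3 correlation. Assume no true effect, equal SDs, a shift s (in SD units) between arms at M0 that is absent at M3, and slope b.

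- Bias of the adjusted effect = −b × s.
- Standard error ≈ √(1 − b²) × √(2/40). This is 0.8 × 0.2236 = 0.179 for b = 0.6 and 0.714 × 0.2236 = 0.160 for b = 0.7.
- Two-sided type I error = P(|Z + bias/SE| > 1.96).

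| Shift s | b = 0.6: size of bias, type I error | b = 0.7: size of bias, type I error |
|---|---|---|
| 0 | 0, 5% | 0, 5% |
| 0.1 SD | 0.06 SD, 6.3% | 0.07 SD, 7.2% |
| 0.2 SD | 0.12 SD, 10.3% | 0.14 SD, 14.2% |
| 0.3 SD | 0.18 SD, 17.2% | 0.21 SD, 26.0% |

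Example: s = 0.2, b = 0.6 gives 0.12/0.179 = 0.67, and P(Z > 1.29) + P(Z < −2.63) = 0.099 + 0.004 = 0.103.

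**Check by simulation** (40 per arm, 10,000 runs per setting). At correlation 0.7 the adjusted analysis rejected in 7.0%, 13.6% and 25.4% of runs for shifts of 0.1, 0.2 and 0.3 SD. Over correlations 0.5 to 0.8 the ranges were 6–9%, 8–22% and 12–42%. With no shift the rate was 4.9–5.4%. A t test on the M3 scores alone stayed at 4.7–5.4% throughout.

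**Direction.** If experimental-arm scores look better at M0 because of allocation, adjustment works against the program. If they look worse, it works in favor.

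**The case against.** The strongest reply is that nothing shows a shift exists. That stands: without one there is no bias, so the claim can only be that adjustment may bias the comparison.

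A reader might infer that participants knew their arm while completing all the scales, or that someone who left on learning the arm would have no secondary baseline. The listed order does not support either. The control-arm step, "The CC participants are notified that they will receive a website access at the end of their participation to this protocol", and the experimental-arm material both come after the scales. Participant awareness during the ZBI, NHP and BDI-2 is therefore not shown, and on the listed order those data would already exist. Nor does the text support calling the baseline table uninterpretable. A reader might also add that change scores would fare worse, but the article plans none.

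The calculation lets the shift vanish by M3. If the same reporting tendency persisted, adjustment would remove part of it: with 0.2 SD at both visits, the adjusted bias is 0.20 − 0.12 = 0.08 SD (b = 0.6) or 0.20 − 0.14 = 0.06 SD (b = 0.7), against 0.20 SD unadjusted. That is fair, but a distortion at M3 comes from the lack of blinding and not from the order at M0.

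Unadjusted tests are already planned alongside the covariance analysis. That also stands, but the article does not say which of the two leads for the secondary outcomes.

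Finally, a fuller protocol could contain a step that withholds allocation. That would reduce the risk; the order, stated in two sections, would remain as it is.

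**Conclusion.** The point holds as a risk to the covariate-adjusted secondary comparisons. It is clearest for the RSCS, the RMBPC and the caregiving interview, and weaker for the self-administered scales. Size and direction are unknown. The range of about 6% to 26% for two-sided type I error rests on an assumed shift of 0.1 to 0.3 SD present at M0 only, an assumed slope of 0.6 to 0.7, and 40 per arm. It also takes the usual order as the one followed.

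A reader might extend this to the main result. The documents do not support that: the PSS-14 is measured before randomization, so its baseline is sound, and the order at M0 does not touch any unadjusted M3 comparison.

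**What to change.** **Anyone still to be enrolled:** keep consent, the PSS-14 and the eligibility check first, then complete the interview and all M0 scales, and only then randomize, train or notify. This fits the same 90-minute visit without extra staff. The small cost is that a few caregivers may complete the battery and then not be randomized.

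**Those already enrolled:** reordering may help few or none. The abstract has current participants finishing in January 2014, and six months of follow-up puts their last M0 visits at about July 2013. For them:

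- state that the M0 secondary scores and interview variables were usually collected after randomization;
- make the main secondary comparison either unadjusted at M3 or adjusted only for the pre-randomization PSS-14 and the stratification factors (gender, spouse or nonspouse), and fix which before the data are analyzed;
- report the analysis adjusted for M0 secondary scores as sensitivity.

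This needs no new data. Its cost is some precision if the M0 secondary scores were in fact undisturbed: for b = 0.6 to 0.7, the unadjusted standard error is 0.224 SD against 0.179 to 0.160 SD.
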